**Results:**

This study received funding in May 2020. Ethics approval was received in June 2020. The recruitment of participants began in June 2020. Participant recruitment is being conducted via social media, web-based communities, and physician referrals. To date, 58 participants have been recruited (intervention group: n=35; control group: n=23). Data collection is expected to conclude by the end of 2020. Analyses (ie, linear regression analysis for continuous outcomes and binomial regression analysis for categorical outcomes) are expected to be completed by February 2021.

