### Outcome Evaluation

Primary outcome measures will be anxiety level based on Generalized Anxiety Disorder-7 (GAD-7) Item Questionnaire scores, depression level based on Patient Health Questionnaire-9 Item scores, resilience level based on Resilience Scale-14 Item Questionnaire scores, and quality of life based on Quality of Life and Enjoyment Questionnaire scores. All questionnaires will be collected directly through the OPTT at baseline, prior to week 5, and after the last session.

In addition to these quantitative measurements, qualitative analyses will be performed to evaluate the efficacy and feasibility of providers delivering e-CBT and participants receiving e-CBT. Health care providers will be asked about the feasibility of providing e-psychotherapy and how it compares to in-person psychotherapy in terms of time commitment, feelings of connectedness to the participant, and any perceived benefits and drawbacks to e-psychotherapy. Information on personal, social, and cultural factors (eg, gender, sexuality, background, supportive resources, structural/social barriers, etc) will be extracted from focus groups using an interpretive phenomenological analysis approach. Additionally, participants will be asked about their experiences with using the OPTT and their positive or negative experiences with the e-CBT program. Program adherence and completion rates will also be recorded and reported.

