### Data Analysis

Initially, all data will be examined for missing, nonsensical, and outlying variables. Missing data will be treated as missing and not imputed. This will be analyzed on a per-protocol basis. Given the likelihood of participant drop out or withdrawal, we have purposely oversampled our study and control groups to obtain meaningful and statistically significant results at the end of the study. Based on our previous experience with CBT and e-CBT in similar patient populations, we anticipate that up to 30% of participants will drop out by the end of the treatment or TAU phases. Using GAD-7 questionnaire scores as the primary outcome means that a 30% change is considered clinically significant. Therefore, a sample size of 40 participants in each arm of the study will be sufficient for detecting significant results (ie, *P*=.05 and a power of 0.95). In addition, an intention-to-treat analysis will be performed to evaluate completion rates and the clinical effects of participants leaving the trial before completion.

Data collection will occur at 3 separate time points, as follows: at baseline (ie, preintervention), in the middle of the study (ie, week 5), and immediately at postintervention (ie, week 9). Mann-Whitney U tests will be used to compare baseline demographic data between individuals who drop out and those who finish the e-CBT program, and any fundamental differences between completers and noncompleters will be identified. A linear regression analysis for continuous outcomes and binomial regression analysis for categorical outcomes will be performed to identify variables associated with the 2 outcome measures over the 3 measurement time points and to compare the differences between study arms. These analyses will be controlled for demographic variables, such as age and gender.

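### The arm comparison uses plain regression over baseline, week 5 and week 9, with no term for within-person correlation and no adjustment for baseline score

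*Protocol article*

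**What the plan says.** The Data Analysis section of the protocol article states: "A linear regression analysis for continuous outcomes and binomial regression analysis for categorical outcomes will be performed". The stated purpose is "to identify variables associated with the 2 outcome measures over the 3 measurement time points and to compare the differences between study arms". The same section defines the three time points as baseline, week 5 and week 9, so the pre-treatment measurement is one of them. On covariates it says: "These analyses will be controlled for demographic variables, such as age and gender".

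The Outcome Evaluation section confirms that the same people are measured repeatedly: "All questionnaires will be collected directly through the OPTT at baseline, prior to week 5, and after the last session". The Results paragraph of the abstract repeats the models without qualification: "linear regression analysis for continuous outcomes and binomial regression analysis for categorical outcomes".

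No random effect, GEE, clustered or robust standard error, time term or arm-by-time term appears anywhere in the article, and the baseline score is not named as a covariate. The Participants section describes the control group as eligible patients who did not want the e-psychotherapy programme.

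**The concern.** The regressions named assume independent observations. Three GAD-7 scores from one person are not independent. If they enter one regression as separate rows, the reported standard errors are wrong, and the direction depends on the coefficient read. A pooled arm effect also averages in a time point at which treatment cannot have acted.

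If instead a regression is run at each time point, that problem disappears and another remains. Arms formed by patient choice may differ in severity at entry, and the week 5 and week 9 comparisons would not use the baseline score that the trial collects.

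The same sentence also combines a search for variables associated with outcome with the comparison of arms, so no coefficient or time point is marked as the answer to the efficacy hypothesis. This is the only between-arm efficacy analysis that the article describes.

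**Working it through.** **The plan's own figure.** The Data Analysis section gives 40 per arm for alpha 0.05 and power 0.95, on the basis that "a 30% change is considered clinically significant". This cannot be reproduced, because no baseline mean or SD is given. Solved backwards (two-sided), 40 per arm implies a standardized difference of (1.960 + 1.645) × √(2/40) = 0.81. With the 30% dropout the plan allows for, 40 × 0.70 = 28 per arm, which implies 3.605 × √(2/28) = 0.96. The present point does not depend on these figures.

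**Inputs.** Three measurements per person come from the article. The within-person correlation ρ is not given. I assume equal correlation between all pairs, with ρ from 0.4 to 0.7, and equal variance at each time point.

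**Reading A: the three scores are pooled in one regression.**

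*Arm main effect.* With n per arm and variance σ², ordinary regression takes the variance of the arm difference as (2σ²/n)/3. The true variance is (2σ²/n)(1 + 2ρ)/3. The ratio of true to reported standard error is √(1 + 2ρ). With unequal arms, 2/n becomes 1/n₁ + 1/n₂ in both expressions and cancels, so the ratio does not depend on sample size or allocation.

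*Arm-by-week-9 term (week 9 against baseline).* The reported variance is 2σ²(2/n) and the true variance is 2σ²(1 − ρ)(2/n). The ratio of standard errors is √(1 − ρ).

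The true type I error at a nominal 5% is 2[1 − Φ(1.96/ratio)].

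| ρ (assumed) | Main effect: true/reported SE | Type I error | Arm-by-week-9: true/reported SE | Type I error |
|---|---|---|---|---|
| 0.4 | √1.8 = 1.34 | 14.4% | √0.6 = 0.77 | 1.1% |
| 0.5 | √2.0 = 1.41 | 16.6% | √0.5 = 0.71 | 0.6% |
| 0.7 | √2.4 = 1.55 | 20.6% | √0.3 = 0.55 | 0.03% |

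At ρ = 0.3 the main-effect type I error is still 12.1%.

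A simulation with no treatment effect, 28 per arm and 4,000 runs agrees. At ρ = 0.5 and 0.7 the main effect rejected in 16.8% and 21.1% of runs, and the arm-by-week-9 term in 0.8% and 0.05%. A week 9 regression with baseline as covariate rejected in 5.5% and 4.8%, which is nominal.

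*Dilution of the pooled arm effect.* If the effect builds linearly (0, 0.5, 1), the average is 1.5/3 = 50% of the week 9 effect. If it is complete by week 5 (0, 1, 1), the average is 2/3 = 67%.

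**Reading B: one regression per time point.** Each person contributes one row, so the standard errors are valid. The regression at baseline compares arms before treatment. Those at week 5 and week 9 carry over any difference at entry. If the later score depends on the baseline score with slope ρ in both arms, a baseline difference of 1 point leaves ρ × 1 = 0.4 to 0.7 points at week 9 with no treatment effect at all. The size of any baseline difference is not known from the article.

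**The case against.** The strongest reply is that the article never says the three rows per person are stacked. Separate regressions, a regression on change, or loose shorthand for a longitudinal model would all fit the sentence, and covariance structure is often left to an analysis plan. This stands in part. A reader might infer that the P values for efficacy are certain to be wrong; the text does not support that, and the standard-error result holds only under pooling. But this is not mere silence: the article names the models, the time points they span, their purpose and the type of covariate.

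The two errors under pooling are also opposite and cannot both apply. For a hypothesis about improvement relative to control, arm-by-time is the more natural term, and it is conservative. So the inflation to 14% to 21% should not be presented as the expected result.

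A reader might also infer that having baseline among the outcomes is itself an error. It is not: valid longitudinal models keep baseline in the response. The standard-error problem comes from ignoring correlation. Baseline does harm only when it is averaged into a single arm effect.

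Finally, it is tempting to state how much power the fix would recover. The documents give no SD or standardized effect, and the usual gain from baseline adjustment presumes balanced baselines, which this allocation does not provide. Self-selection into arms may well be the larger threat, and no covariance structure corrects it. The authors acknowledge the nonrandomized design as a limitation.

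**Conclusion.** The point holds conditionally. As written, the efficacy model has no provision for repeated measures and no baseline-score adjustment, and it falls short on either reading examined here.

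- **Pooled:** the standard errors are wrong. For ρ of 0.4 to 0.7, the standard error of the arm main effect is understated by 1.34 to 1.55 times (type I error about 14% to 21%), and that effect shrinks to between half and two thirds of the week 9 effect under the two time courses shown. An arm-by-week-9 term has type I error of about 1% or less and loses power.
- **Separate regressions:** the standard errors are valid, but comparisons of people who accepted the programme with people who declined it ignore their scores at entry.

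The figures rest on an assumed equal within-person correlation, complete data and a continuous outcome. No size was worked out for the binomial models, and no power gain can be stated from the documents.

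**What to change.** Replace the regression sentence in the Data Analysis section, and the matching phrase in the abstract, with one of the following:

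- a mixed model or GEE with participant as the cluster, for the week 5 and week 9 scores, with arm, time and arm-by-time, adjusted for baseline score and the demographic variables already listed; or
- a regression of the week 9 score on arm, adjusted for the same covariates.

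In either case, name the week 9 arm difference with its 95% CI as the primary contrast. For categorical outcomes, use the analogous GEE or a single week 9 model. Report variables associated with outcome separately, as exploratory. While the sentence is open, reconcile its reference to two outcome measures with the four primary measures in the Outcome Evaluation section.

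State alongside the result that baseline adjustment does not remove all selection bias from nonrandomized allocation.

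The cost is analysis wording only: the baseline scores are already collected, the software is standard, and no new data are needed.

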## Methods

### Study Design

This clinical trial has a nonrandomized controlled trial design. Participants in the intervention group will be offered a 9-week e-CBT program that is tailored to address mental health problems in the context of the COVID-19 pandemic. Qualitative focus groups will be conducted to gather personal demographic information, as well as information about the feasibility of implementing an online psychotherapy clinic. Additionally, quantitative analyses of online psychotherapy treatment efficacy will be conducted using standardized symptomology questionnaires. All procedures have been approved by the Queen’s University Health Sciences and Affiliated Teaching Hospitals Research Ethics Board.

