### Participants

Participants (N=80) aged 18-65 years will be enrolled in the study based on referrals from the Hotel Dieu Hospital and Providence Care Hospital outpatient clinics located in Kingston, Ontario, Canada, and self-referrals from social media and web-based communities. Those referred and interested in participating will provide informed consent before being evaluated by one of the psychiatrists on the research team through a secure video appointment. During this appointment, MDD/GAD diagnoses will be made or confirmed using the Diagnostic and Statistical Manual of Mental Disorders, 5th Edition (DSM-5). Mini-International Neuropsychiatric Interview, Version 7.0.2 DSM-5 will also be administered by a trained research assistant on the team to confirm the diagnosis. Inclusion criteria includes the capacity to consent; a primary diagnosis of GAD or MDD, with symptoms that started or worsened during the COVID-19 pandemic; the ability to speak and read English; and consistent and reliable access to the internet. Exclusion criteria includes active psychosis, acute mania, severe alcohol or substance use disorder, and active suicidal or homicidal ideation. Additionally, to keep the scope of this study focused on the more common challenges that people face during the pandemic, participants will be excluded if mental health problems are secondary to a medical condition. Moreover, if a participant is currently receiving or has received CBT in any format during the past year, they will be excluded to prevent a possible confounding effect between previous CBT treatment and the e-CBT program.

Participants who are eligible for this study will be offered to join the electronic psychotherapy (e-psychotherapy) group. If individuals in this treatment group have been on pharmacotherapy treatment, their medication from 6 weeks prior to the trial and during the 9 weeks of treatment will not get changed. Individuals diagnosed with MDD or GAD who do not wish to participate in the e-psychotherapy group will continue to receive treatment as usual (TAU) and will be part of the control group. TAU is defined as any lifestyle activities and interventions (ie, medication, psychiatric consultation and referrals, exercise, diet, etc) that participants in either group were receiving prior to joining the trial. These activities and interventions will not be changed throughout the course of participants’ participation. Both groups will be stratified by sex, gender, and age.

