## Discussion

Addressing the extensive mental health problems resulting from the COVID-19 pandemic requires rapid and easily accessible solutions. An online psychotherapy clinic with predesigned therapy modules can be used to rapidly scale up clinical capacity to address mental health problems resulting from the COVID-19 pandemic, while also ensuring a high quality of care. That is why, through this study, we emphasize developing and validating a comprehensive solution (ie, engaging and effective content, feedback templates, and clinician training) that can be easily deployed with minimal resources. We are also planning to disseminate the outcomes of our study through publicly accessible media, so other clinicians can easily access and incorporate this solution into their clinical practices in time to meet their patients’ needs. This approach will result in major financial savings for the health care system, as it provides methods for the efficient use of clinicians’ time and the equitable and accessible delivery of care to patients.

It should be noted that our current study design has some limitations, such as the nonrandomized design of the study. In order to address these concerns in a structured format, we are using the “guidance for reporting intervention development studies in health research (GUIDED)” framework [23] and “template for intervention description and replication (TIDieR)” [24] to report our protocols and outcomes (Tables S1 and S2 in Multimedia Appendix 1). We are also planning to start a randomized study in January 2021. Additionally, the electronic mode of care delivery might not be suitable for specific subgroups of patients (eg, older adults or patients who lack experience with related technologies). We hope that through our qualitative focus groups, we will be able to identify each of these subgroups and find suitable remedies for future iterations of our study design (eg, changing the module design so that it is user-friendly for older adults).

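### The control arm is made up of people who declined e-CBT, but the only adjustment stated for the between-arm comparison is demographic, which leaves it open to confounding by clinical factors measured at entry

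*Protocol article*

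**What the plan says.** All of this is in the protocol article.

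- **Design (Study Design):** "This clinical trial has a nonrandomized controlled trial design".
- **How controls arise (Participants):** eligible people are offered the e-psychotherapy group. Of those diagnosed at entry, the people "who do not wish to participate in the e-psychotherapy group will continue to receive treatment as usual (TAU) and will be part of the control" arm.
- **Hypothesis (Background and Rationale):** better quality of life and fewer symptoms in the intervention group than in the control group.
- **Adjustment (Data Analysis):** linear and binomial regressions over three time points compare the arms. The one statement about covariates is "These analyses will be controlled for demographic variables, such as age and gender".
- **Baseline data (Outcome Evaluation):** "All questionnaires will be collected directly through the OPTT at baseline, prior to week 5, and after the last session". These cover anxiety, depression, resilience and quality of life. Under Participants, a psychiatrist makes or confirms the diagnosis at entry and a structured interview confirms it.
- **Stratification (Participants):** "Both groups will be stratified by sex, gender, and age".
- **Medication (Participants):** the condition on the weeks before the trial reads "If individuals in this treatment group have been on pharmacotherapy treatment, their medication from 6 weeks prior to the trial" and names the treatment group alone. The later definition of TAU holds background treatment fixed during participation in either group, without that window.
- **Limitation (Discussion):** the nonrandomized design is acknowledged. The sentence opening "In order to address these concerns in a structured format" then cites two reporting frameworks, and the next one mentions a randomized study planned for January 2021.

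**The concern.** People who accept a nine-week programme of modules and homework may differ from those who decline it in severity, in diagnosis and in the treatment they already receive. Each of these plausibly predicts the week-9 score. Age and gender are weak stand-ins for them, and the stronger variables are established at entry. The only baseline comparison described is of demographic data between people who drop out of e-CBT and people who finish it, so a clinical difference between the arms might not even be displayed.

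What is at stake is the main conclusion. The hypothesis is a between-arm effect, the second objective is phrased as efficacy, and the Results section plans rapid release as a preprint and workshops to help other clinicians deploy the programme. An imbalance at entry could create or hide the difference on which that advice would rest.

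**Working it through.** **The plan's own figures.** The article gives no SD, baseline mean, correlation or baseline gap, so it contains no bias figure to reproduce. Its 40 per arm cannot be confirmed or refuted for the same reason, and the point does not depend on it. Two derived values are useful:

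- Completers at 30% dropout: 40 × 0.7 = 28 per arm, 56 in all.
- Standardised effect implied by power 0.95 and two-sided 0.05: (1.960 + 1.645) × √(2/n), which is 0.81 SD for n = 40 and 0.96 SD for n = 28.

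**Assumptions for the illustration (none is in the article).** Baseline GAD-7 gap D = 2 points, choosers higher; SD 5 at both times; correlation ρ = 0.5 to 0.6; no true effect; baseline mean 12 to 14.

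**Step 1. Both arms regress to the same mean, given baseline.**

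- Final scores: bias = ρD = 0.5 × 2 to 0.6 × 2 = 1.0 to 1.2 points, making e-CBT look worse.
- Change scores: bias = −(1 − ρ)D = −1.0 to −0.8 points, making e-CBT look better.
- Adjusted for baseline: 0.

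If decliners are the more severe group, every sign reverses.

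**Step 2. The arms come from populations whose severity differs stably.**

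- Final scores: bias = D = 2 points.
- Change scores: 0.
- Adjusted for baseline: D − ρD = (1 − ρ)D = 0.8 to 1.0 points.

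This is Lord's paradox. Neither change scores nor baseline adjustment is safe under both assumptions, while the unadjusted final score is biased under both.

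**Step 3. Size against the target.** A 30% change on a baseline of 12 to 14 is 3.6 to 4.2 points. The Step 1 biases run from 0.8/4.2 = 19% to 1.2/3.6 = 33% of it.

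**Step 4. False-positive rate, Step 1 case, 28 per arm.** For final scores SE = 5 × √(2/28) = 1.34. A bias of 1.0 shifts the test statistic by 1.0/1.34 = 0.75, and P(|Z + 0.75| > 1.96) is about 0.12 instead of 0.05.

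**Step 5. Simulation.** 4,000 trials per setting were run with no true effect and least squares adjusted for age and sex, with and without the baseline score. Baseline imbalance was 0.3 to 0.5 SD and correlation 0.5 to 0.7.

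| Completers per arm | Bias, age and sex only | Type I error, age and sex only | Type I error, baseline added |
|---|---|---|---|
| 28 | 0.15 to 0.35 SD | 8% to 26% | 4.4% to 5.2% |
| 40 | 0.15 to 0.35 SD | 10.5% to 33% | 4.4% to 5.4% |

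The simulated imbalance acts only through the baseline score, so the clean last column follows from the Step 1 assumption and does not test it. The larger sample has the higher error rate, because the bias stays while the standard error shrinks.

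**Step 6. Precision.** Adjusting a final score for its baseline removes ρ² of the residual variance: 0.25 to 0.36.

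**The case against.** **Baseline may already be in the model.** The regression covers three time points, one of which is baseline, so an arm-by-time contrast could carry baseline level. A condensed article may also leave the covariate list to a fuller document. This stands in part. A reader might infer that baseline is excluded, and the text does not say so; it says only that demographics are controlled and names nothing else. But no arm-by-time contrast is stated, and it would amount to the change-score case in Step 1. Nor would it deal with change that differs by diagnosis or background treatment. The article does state a class of covariates, and the words introducing age and gender as examples leave that list open only within demographics.

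**The size is assumed.** This stands in full. A reader might infer that the effect is confounded by a known amount in a known direction. The article supports only that the comparison is open to confounding: it supplies none of the inputs, and Steps 1 and 2 show that the sign depends on the outcome form and on an untestable assumption.

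**The limitation is acknowledged.** True, and the Discussion offers a later randomized study as well as reporting frameworks. Neither changes the analysis of this trial.

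**Stratification.** A reader might infer a false claim of balanced allocation. The sentence does not mention allocation and could describe recruitment, analysis or reporting. It needs clarifying, not deleting. On any reading it covers demographics only.

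**Medication.** The two statements need not contradict each other, since one may simply add a condition for one arm. The asymmetry is nevertheless unexplained, and it allows medication timing before baseline to differ by arm.

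**A long covariate list or propensity weighting would be too much** for about 56 completers, with 35 and 23 recruited at publication. This stands and limits the fix.

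**Conclusion.** The concern holds in this form: arm is self-selected, the stated adjustment is demographic, and the article does not say how baseline score, diagnosis or background treatment is handled, although baseline scores and diagnosis are obtained at entry. The between-arm comparison is open to confounding of unknown size and direction. Under the assumptions listed, the bias is about 1.0 to 1.2 GAD-7 points on final scores or 0.8 to 1.0 points in the opposite direction on change scores, roughly a fifth to a third of the 30% target. Those figures show that the issue could matter; they do not estimate what happened in this trial. Measured covariates would reduce the problem without removing it, because motivation and treatment preference are not measured.

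**What to change.** 1. **Data Analysis:** replace the adjustment sentence with a short prespecified set: baseline value of the outcome, primary diagnosis (MDD or GAD), medication status at baseline, age and gender. State how baseline enters the three-time-point model.
2. **Baseline table:** compare the arms, clinical variables included, using standardised differences.
3. **Sensitivity analysis:** repeat the comparison on change scores, because baseline adjustment in self-selected groups rests on the Step 1 assumption. Report both results. Propensity weighting is optional only.
4. **Participants:** say what the stratification refers to and that it does not control self-selection. Reconcile the six-week pre-trial medication statement, which names the treatment group, with the statement covering either group.
5. **Conclusions:** report an adjusted association and name unmeasured motivation as a remaining explanation.

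**Cost.** This is a change of wording, using the baseline scores, the entry diagnosis and the medication status that the plan's own definition of TAU already requires. If each covariate takes one term, the model goes from 4 parameters (intercept, arm, age, gender) to 7, leaving 56 − 7 = 49 residual degrees of freedom instead of 52. Binomial models tolerate fewer terms and may need a shorter list. The other cost is a more cautious conclusion.
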